### Safety

There is no reason to assume that this study will lead to an excess of adverse events. The treatment consists of advice from the GP and offer of referral to a weight management service, neither of which seem likely to create harm. We are aiming to recruit participants who are not specifically motivated to lose weight and therefore intend to keep participant burden to a minimum. Therefore, we will not monitor the occurrence of adverse events by trial arm.

We recognize that follow-up of participants requires us to behave sensitively and that, in a trial of this size, some participants will suffer serious health events or other misfortunes that will come to light in a follow-up telephone call. To ensure that future follow-up attempts are appropriate, we will log these events in the critical events log of the case report form (CRF).

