#### An ‘assistance-orientated’ treatment (intervention)

The GPs assistance-orientated treatment (that is, practical support) is aimed to last no more than a few seconds: “Did you know that the best way to lose weight is to go to Slimming World? I can refer you now for free on the NHS if you would like.” The choice of weight management service will mainly be determined by availability in the local area. In the Lighten Up trial, WW, RC, and SW each performed better than the control group [13].

If the person agrees to referral to the CWMS, the GP will ask the participant to make an appointment at reception to return in a month: “I know it can be difficult to lose weight, so I’d like you to return in a month to see how you’re getting on”. If the participant wants to try weight loss without assistance, the GP might say: “It’s fine for you to try to lose weight on your own but I know it’s hard. Would you make an appointment to return in a month to see how you are getting on?” This provides an opportunity to re-refer those who accepted referral but did not attend, refer those who tried to lose weight on their own but did not do well, prescribe orlistat to those who have followed the treatment program but not succeeded (in line with NICE guidance), and it lets the patient know their doctor is taking this seriously [30]. If the participant wants to discuss this with their GP, the GP will encourage the participant to make another appointment to do so (English GPs have 10 minutes per consultation).

Outside the context of the trial, we would envisage that the GP would make a referral to the weight management service in the same way s/he makes referrals to other services. We could envisage a system of direct booking, where the availability and days/times of local services are shown online on the GPs computer. However, because referral to weight management is uncommon, our GPs and patient representatives advised us it would be better to ask the research team to do this. We will aim for the RA in the practice to hold details of local groups that are available and make a booking immediately, to capitalize on the patient’s impulse to act. If this is not possible, we will arrange to telephone the participant at the earliest convenience with details of the options available.

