### Data monitoring committee

We do not propose that a data monitoring and ethics committee would be useful, based on examples from http://www.ct-toolkit.ac.uk/ as this is an unblinded study with no substantial risk and no early termination rules. The final decision was made by the TSC, who agreed that it would not be useful for this trial and that they would adopt the role if required.

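### On a prior expectation of low harm the plan forgoes a by-arm look at adverse events, although serious health events are already logged in the CRF

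*Protocol article*

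**What the plan says.** The Safety section opens with an expectation: "There is no reason to assume that this study will lead to an excess of adverse events". It describes treatment as GP advice plus an offered referral and judges both unlikely to do harm. It adds that the load on participants should be kept low, and concludes that "we will not monitor the occurrence of adverse events by trial arm".

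The next paragraph accepts that, in a trial of this size, some participants will have serious health problems or other mishaps, which "will come to light in a follow-up telephone call". The instruction for these is: "we will log these events in the critical events log of the case report form". The stated reason for the log is not safety analysis but contact management: "To ensure that future follow-up attempts are appropriate".

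Three other places bear on this:

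- The section on the assistance-orientated treatment provides for a return visit at about one month. At that visit the GP may, among other things, "prescribe orlistat to those who have followed the treatment program but not succeeded". The Background also mentions this drug treatment and expects it to be uncommon in the trial.
- The Data monitoring committee section decides against a committee because "this is an unblinded study with no substantial risk" and there are no early stopping rules. The steering committee took that decision and agreed to take on the role if it were needed.
- The objectives, the outcome lists and the Description of statistical methods contain no comparison of harms.

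**The concern.** This is a stated rule, not a detail left to the analysis plan. Burden is a good reason for not asking participants about adverse events. It does not cover entries already in the CRF, because splitting those by allocation needs no further contact.

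The low-risk reasoning also rests on a narrower account of treatment than the rest of the protocol gives. The Safety section speaks of advice and referral. Elsewhere the intervention arm has a weight-management program (typically 12 sessions), a scheduled review and possible drug prescribing.

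At stake is what can be said beside the efficacy result. The Discussion and the Rationale present the trial as a possible basis for widespread treatment and for inclusion in the GP pay-for-performance scheme. A decision-maker will ask whether serious events were similar in the two arms. The plan gives the report no basis for an answer, even a cautious one.

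**Working it through.** **1. The plan's own figure.** The Safety section gives no number. The only related figure is the sample size (Number of participants), which fixes the denominators.

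- Intervention arm mean loss: 0.30 × 3.46 + 0.70 × 0.05 = 1.073 kg.
- Control arm mean loss: 0.10 × 1.16 + 0.90 × 0.05 = 0.161 kg.
- Difference: 0.912 kg, or 0.91 kg from the rounded means.
- With SD 6.0 kg, 90% power and 5% two-sided error (sidedness is not stated, so this is an assumption), n per arm = 2 × 6.0² × (1.960 + 1.282)² / difference². This gives 910 with 0.912 kg and 914 with 0.91 kg.

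The stated 912 per arm is reproduced. It was set for weight change and says nothing about harms.

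**2. Do the stated reasons cover the choice?**

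| Reason in the plan | What it covers | What it leaves open |
|---|---|---|
| Low burden on participants | Not soliciting adverse events | Tabulating events already logged |
| Advice and referral are unlikely to harm | A light approach to collection | The review visit and possible orlistat, which the Safety section does not mention |
| Steering committee can act as monitor if required | No standing committee | What by-arm information would show that it is required |

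**3. What a by-arm table could show.** The document gives no event rate, so control-arm rates of 1% to 10% over 12 months are assumed. Two denominators are used: all 912 per arm, and 0.70 × 912 = 638. The second applies the assumed follow-up figure to the calls, for which no separate contact rate is given.

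- 95% CI half-width for the risk difference, with equal rates p: 1.96 × √(2p(1 − p)/n). For p = 0.05 and n = 912: 1.96 × √(0.095/912) = 1.96 × 0.0102 = 0.020.
- Detectable rate: the p₂ that gives 80% power at two-sided 5% in the normal-approximation test of two proportions, with pooled variance under the null.

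| Assumed control rate | Expected events, n = 912 | CI half-width, n = 912 | Detectable rate (ratio), n = 912 | CI half-width, n = 638 | Detectable ratio, n = 638 |
|---|---|---|---|---|---|
| 1% | 9 | 0.9 points | 2.8% (2.8) | 1.1 points | 3.3 |
| 2% | 18 | 1.3 points | 4.3% (2.1) | 1.5 points | 2.4 |
| 5% | 46 | 2.0 points | 8.3% (1.65) | 2.4 points | 1.8 |
| 10% | 91 | 2.75 points | 14.3% (1.4) | 3.3 points | 1.5 |

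At 1% only about a threefold difference could be detected. At 5% to 10% the interval is narrow enough to inform.

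**4. Would the arms be comparable?** Both have the same planned 3- and 12-month contacts and the same limit of three contact attempts. The Unblinding section says that patients and follow-up assessors will be blinded to allocation. This supports similar, though incomplete, capture. It does not guarantee it: the Background warns of differential follow-up, and the calls ask what participants did about their weight, which could hint at allocation.

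**The case against.** The strongest reply is that this is a deliberate, explained choice in a low-risk trial.

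- **The log has another purpose.** It exists to keep later contact appropriate and takes in misfortunes that are not medical. Logging without monitoring by arm is therefore not a contradiction. This stands.
- **Monitoring is not the same as tabulating.** The sentence need not forbid a descriptive table at the end, and an analysis plan that is not shown may include one. This stands in part. The protocol sentence is the only rule on the page and it points away from a by-arm look. If a final table is intended, the sentence should say so.
- **The exposure contrast can be overstated.** Orlistat is expected to be uncommon, and the GP training modules include a dedicated weight consultation for the control arm too. This stands. The scheduled one-month review is still described only for the intervention arm.
- **Incidental data do not deserve formal precision.** An interval does not reflect under-counting or unequal capture. This stands as a caveat on the table, not as a reason to withhold it.

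A reader might go further and infer that the protocol claims the intervention does no harm and then denies itself the evidence. The text does not support that. It offers a hedged prior expectation as the reason for a monitoring choice, lists no safety objective and promises no safety conclusion. A reader might also want an upper bound on the event rate from zero logged events. That does not fit either: the protocol expects some events, and an incidental log cannot turn an absence of entries into an absence of events.

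**Conclusion.** The point holds as a low-cost improvement, not as an internal error. On a prior expectation of low harm, the plan forgoes by-arm information on harms that it will partly hold, and the burden argument does not reach data already recorded. The trial would then offer no randomized information on harms with its case for roll-out.

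The gain is modest. At assumed event rates of 1% to 10%, the 95% interval for the risk difference would extend about 0.9 to 2.75 points either side with 912 per arm, or 1.1 to 3.3 points with 638. These figures rest on assumed rates and on similar capture in both arms. They cannot allow for events that never reach the log, so the table could not establish absence of harm. The sample size and the primary analysis are unaffected.

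**What to change.** Keep the light data collection. Replace the sentence on not monitoring by arm with a statement along these lines:

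- Serious health events in the critical events log, including any deaths that come to light, will be classified by someone without knowledge of arm.
- At final analysis they will be tabulated descriptively by arm: participants with an event, number reached, and difference in proportions with a 95% CI. The table will be shown to the steering committee.
- The table will state that ascertainment was incidental, incomplete and dependent on follow-up, and that it cannot establish absence of harm.

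Separately, reconcile the Safety section's description of treatment as advice and referral with the Background and the assistance-orientated treatment section, which allow for a review visit and possible orlistat prescribing in the intervention arm.

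The cost is one table and the blinded classification, with no new data and no extra participant contact. The downside is that the log under-counts events and the comparison is imprecise when events are rare, so the caveat must appear with the table.

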### Statistics and analysis

#### Number of participants

The primary outcome will be weight change at 12 months. The following figures assume a 70% follow-up achieved in the Lighten Up trial and use the (conservative) ITT BOCF figures. We assume that 30% in the CWMS arm will take up referral and achieve the mean loss seen in our trial of the same intervention at 1 year (3.46 kg with BOCF for missing outcome data) and that 10% in the control arm will try to lose weight and achieve the mean loss seen in the Lighten Up trial (1.16 kg). The Prospective Studies Collaboration showed that obese people observed over a few years lose a little weight on average, at about 50 g/year [2]. These assumptions give mean weight loss of 1.07 kg versus 0.16 kg. The standard deviation for weight change was about 6.0 kg in both our Lighten Up and the Jebb trial [14,15]. On these assumptions, with 90% power and 5% type I error, we would need to randomize 912 people to each arm: 1,824 in total.

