Keeping a register of all adults with obesity in a practice is now also a clinical management area of the QOF. However, GPs are required only to record weight and there are no indicators related to interventions, even in the case of obesity in diabetes. This reflects the lack of evidence from RCTs for opportunistic intervention and referral for weight management interventions that might be practicable in primary care. Unlike for smoking, GPs do not record whether or not they discuss weight management with their patients, there is no national surveillance system for recording brief interventions and there is no NHS weight management service, akin to the NHS Stop Smoking Service.

Two recent RCTs investigated practicable interventions for obesity management in primary care. In the Birmingham Lighten Up trial, 740 patients were randomized to one of six interventions or minimal control [13,14]. The interventions were 3 month programs with Weight Watchers (WW), Slimming World (SW), Rosemary Conley (RC), Size Down (an NHS group program), GPs and pharmacies. Dieticians trained GPs and pharmacists in weight management. Using intention-to-treat (ITT) analysis with (the conservative) baseline observation carried forward (BOCF), GP and pharmacy care achieved similar weight loss to the minimal control (1 kg at one year); that is, they were ineffective. However, those receiving WW, SW and RC lost 4 to 5 kg by 12 weeks, and at 1 year achieved 2 kg (SW and RC) to 3.5 kg (WW) weight loss. These results are similar to those from the trial by Jebb [15], where 772 participants randomized to 12 months WW or GP care achieved a weight loss of 4.0 kg and 1.6 kg, respectively, at 1 year. Over two-thirds of English primary care trusts (PCTs) currently contract with commercial weight management services (CWMS), costing PCTs about £50 per patient to provide a free (to the patient) 12-week treatment course ‘on prescription’. An earlier systematic review concluded that there was sufficient evidence of effectiveness for WW but not the other main CWMS in the US [16]. Thus, CWMS, and WW in particular, provide an evidence-based service analogous to the NHS Stop Smoking Service and to which patients can be referred in the NHS.

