To examine the fidelity of the interventions, we will seek the permission of both participants and GPs to audio-record the brief intervention component of a proportion of consultations (n = 5) by each GP. Most GPs will be familiar with recording their consultations as part of their training and most patients agree to this. To examine for evidence of consultation distortion, we will take the first 30 participants who have been recorded and compare the immediate post-consultation ratings of helpfulness and appropriateness to those not recorded. If evidence of distortion is found, we will not continue the recordings. Fidelity in the intervention group will be assessed by recording whether or not an offer of referral was made and whether or not there was supporting discussion (for example, encouragement to attend, advice on the superiority of the service over trying alone). Fidelity in the control group will be assessed on whether advice was given that linked weight loss to improved health and that no offer of referral to weight management was made.

Participants in the assistance-orientated intervention (that is, practical support) group will be offered referral to an evidence-based CWMS available in the NHS; for example, SW or RC. Immediately after the GP appointment, RAs at the GP practice will provide the intervention group participants with their weight management referral packs and assist booking the participant’s first appointment. Group leaders of these CWMS undertake rigorous weight management training through their organization and are expected to follow standard procedures.

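### The sample size credits every referral taker with what appears to be the Weight Watchers result, but the services the protocol names are Slimming World and Rosemary Conley; the 90% power depends on the provider mix

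*Protocol article*

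**What the plan says.** Number of participants builds each arm's mean from a mixture. In the intervention arm, the 30% who take up referral are assumed to "achieve the mean loss seen in our trial of the same intervention at 1 year (3.46 kg with BOCF for missing outcome data" (BOCF is baseline observation carried forward). In the control arm, 10% are assumed to try and to lose 1.16 kg. Background drift is about 50 g a year. The resulting means are 1.07 kg and 0.16 kg, the SD is 6.0 kg, and the conclusion is that "with 90% power and 5% type I error, we would need to randomize 912 people to each arm: 1,824 in total".

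The Background reports the earlier trial (Lighten Up) by provider, by intention to treat with BOCF: the commercial services "at 1 year achieved 2 kg (SW and RC) to 3.5 kg (WW) weight loss".

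For the present trial, the section on the assistance-orientated treatment scripts the GP's words as "Did you know that the best way to lose weight is to go to Slimming World". Treatment providers describes referral to an evidence-based service "available in the NHS; for example, SW or RC". The assistance-orientated section also says that the service will mainly depend on what is available locally, and notes that WW, RC and SW each beat control in the earlier trial.

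**The concern.** The 3.46 kg is presented as the result of the same intervention. By the protocol's own provider figures it fits only one of the three commercial services, and that one is neither in the GP script nor among the examples under Treatment providers. The two services that are named achieved a little over half as much, on the same trial, time point and missing-data rule.

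The target difference of 0.91 kg comes almost entirely from this input, since 0.30 × 3.46 = 1.038 kg of the 1.073 kg intervention mean. If most referrals go to SW or RC, the trial has much less than the stated chance of detecting the effect its own figures imply. A reader who trusts the 90% could then take a non-significant result as stronger evidence against brief referral than it is.

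**Working it through.** **Inputs.** From Number of participants: uptake 30%; loss among takers 3.46 kg; control triers 10%, losing 1.16 kg; drift 0.05 kg for everyone else; SD 6.0 kg; 912 per arm; power 90%; type I error 5% (taken as two-sided, which reproduces the stated size; one-sided would give 745 per arm). From the Background: 2 kg for SW and RC, 3.5 kg for WW.

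**Source of the 3.46 kg.** Number of participants does not name the service. It speaks of the authors' own trial and, a few lines later, of their Lighten Up trial. Among the Lighten Up results in the Background, only WW (3.5 kg) agrees with 3.46 kg. The other cited trial gave 4.0 kg with 12 months of WW, which does not agree.

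**The plan's own figure.**
- Intervention mean: 0.30 × 3.46 + 0.70 × 0.05 = 1.073 kg
- Control mean: 0.10 × 1.16 + 0.90 × 0.05 = 0.161 kg
- Difference: 0.912 kg (0.91 from the rounded means)
- n per arm = 2 × 6.0² × (1.960 + 1.282)² / 0.912² = 910, or 914 with 0.91

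The stated 912 is reproduced. Power at 912 per arm is 90.1% (difference 0.912) or 90.0% (0.91). There is no inflation for the 30% lost to follow-up, which is consistent with BOCF keeping everyone in the analysis.

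**With 2 kg in place of 3.46 kg, all else unchanged.**
- Intervention mean: 0.30 × 2.0 + 0.70 × 0.05 = 0.635 kg
- Difference: 0.635 − 0.161 = 0.474 kg
- SE = 6.0 × √(2/912) = 0.281 kg
- Power = Φ(0.474/0.281 − 1.960) ≈ 39%

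**By share w of referrals going to WW.** The shares are assumed; the protocol gives none. Loss among takers = w × 3.46 + (1 − w) × 2.0.

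| WW share | Loss among takers (kg) | Difference (kg) | Power at 912 per arm |
|---|---|---|---|
| 0% | 2.000 | 0.474 | 39% |
| 25% | 2.365 | 0.584 | 54.6% |
| 50% | 2.730 | 0.693 | 69.4% |
| 75% | 3.095 | 0.803 | 81.5% |
| 100% | 3.460 | 0.912 | 90% |

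**Rounding of the 2 kg.** If it was rounded to the nearest half kilogram (1.75 to 2.25 kg), power with no WW referrals is 29% to 50%. If rounded to the nearest kilogram (1.5 to 2.5 kg), it is 21% to 60%. Neither range reaches 90%.

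**Uptake needed at 2 kg.** Solving 2.0u + 0.05(1 − u) − 0.161 = 0.912 gives u = 1.023/1.95 = 52%, against the 30% assumed.

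**The case against.** **WW is within scope.** SW and RC are introduced only as examples, local availability mainly decides, and the Background singles out WW as an evidence-based service to which patients can be referred. This stands. A reader might infer that the trial will refer only to SW or RC and so has 39% power. The documents do not support that: they give no provider mix, and 39% is the case with no WW referrals at all. What survives is that any mix short of all WW gives less than 90% with the other inputs fixed, and the protocol does not justify assuming all WW.

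**Other inputs may be conservative.** The earlier figures are means over everyone allocated, whereas here they are applied only to those who take up referral, whose loss may be larger. If, as an assumption, 80% of those allocated attended and the rest lost nothing, 2.0 kg becomes 2.0/0.8 = 2.5 kg and power is 60%. Likewise, people who decline referral get only the 0.05 kg drift, although they are invited back after a month. Giving them the control mean of 0.161 kg (again an assumption) makes the difference 0.30 × 2.0 + 0.70 × 0.161 − 0.161 = 0.552 kg and power about 50%. These points are fair and are a further reason not to treat 39% as established. Neither is argued in the protocol, and neither alone restores 90%.

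**ANCOVA may add power.** Reaching 90% at 0.474 kg would need a residual SD of about 3.1 kg, so baseline weight would have to explain 1 − (3.12/6.0)² = 73% of the variance in weight change. Nothing in the protocol suggests that.

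**Nothing is miscalculated.** Correct. The issue is the choice and labelling of one input.

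**Conclusion.** The point holds in conditional form. The protocol describes as the same intervention a result that, by its own provider figures, fits only WW, while the services it names achieved about 2 kg on the same basis. With all other assumptions fixed, power at 912 per arm runs from about 39% (no WW referrals, difference 0.47 kg) to 90% (all WW, difference 0.91 kg).

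This rests on three things: reading 3.46 kg as the WW result, which is inferred from the match with 3.5 kg; taking the rounded 2 kg at face value; and leaving uptake, control loss, drift and SD as stated. It does not show an arithmetic error, and it does not show that the trial has 39% power. The primary analysis is unaffected. What needs correcting is the stated basis for the sample size and the unconditional 90%.

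**What to change.** In Number of participants:

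1. State which service the 3.46 kg comes from (WW, on the Background's figures).
2. Remove the description of it as the same intervention, or justify applying it to the services used in this trial.
3. Say that 912 per arm gives 90% power for a 0.91 kg difference at SD 6.0 kg, and that this difference assumes takers lose 3.46 kg.
4. Add the expected difference and power for the expected provider mix, with a short table by WW share. Show the all-SW/RC case (0.47 kg, about 39%) as conditional on no WW referrals and on the other inputs being unchanged.

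The cost is a few sentences and a small table, and a less favourable power statement. Recruitment had already begun (Trial status), but the change needs no extra participants and leaves the referral rules, randomization, endpoint and primary analysis as they are.
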